**Methods:**

Thirty participants will be randomly distributed between 1) BFR-RT and 2) control (CTRL). Assessments will occur at three time points: before the training intervention (0 W), after 12 weeks (12 W), and at follow-up (24 W). The following variables will be assessed: Child-Pugh classification; MELD score; SF-36 questionnaire; fatigue severity index; 6-min walk test; timed-up and go; 30-s sitting and rising test; dietary record; one-repetition maximum (1-RM) strength test (knee extension exercise); and vastus lateralis’ cross-sectional area, Pennation angle, and fascicle length. The BFR-RT group will undergo 12 weeks of knee extension exercise (1 × 30 repetitions and 3 × 15 repetitions at 20% 1-RM and 50% of total blood flow occlusion pressure), with two sessions per week. Data normality will be assessed using the Shapiro-Wilk test. In case of normal distribution, a one-way repeated measures analysis of variance will be implemented to test for differences in baseline values. A mixed model then will be applied for each dependent variable. In case of non-normal data distribution, a Kruskal–Wallis test will be implemented to test for differences in baseline values. Next, the Friedman test will be used to analyze repeated measures. Within- and between-group effect sizes will be calculated using Cohen’s *d* for each outcome. Finally, the minimal clinically important difference will be analyzed with distribution-based methods.

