## Data analysis

Following visual inspection, data normality will be assessed using the Shapiro-Wilk test. In case of normal distribution, a one-way repeated measures analysis of variance (ANOVA) will be implemented to test for differences in baseline values. Then, a mixed model will be applied for each dependent variable (Child-Pugh class, MELD score, SF-36 and FSS scores, dietary records, TUG, 6MWT, SRT, 1-RM, CSA, PA and FL), having group (BFR-RT and CTRL) and time (0 W, 12 W and 24 W) as fixed factors, and participants as random factors. In case of non-normal data distribution, a Kruskal–Wallis test will be implemented to test for differences in baseline values. Then, the Friedman test will be used to analyze repeated measures. To avoid multiplicity interference on data analysis, adjusted *p* values will be calculated for all variables. Adjusted *p* values will be calculated using Hommel’s procedure, and both adjusted and non-adjusted values will be reported. Additionally, within-group (0-12 W and 0-24 W changes) and between-group effect sizes will be calculated using Cohen’s *d* [33] for each outcome. Finally, the minimal clinically important difference will be analyzed with distribution-based methods [34]. Statistical analysis will be carried out using SAS 9.3 software (SAS institute Inc., Cary, NC).

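### As written, the mixed model implies compound symmetry, so one pooled error serves both the 0-12 W and the 0-24 W change; if the three visits are not exchangeable, those tests miss their nominal level in a direction the documents cannot settle.

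*Protocol article*

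**What the plan says.** Under Data analysis, when data are judged normal, a mixed model is fitted to each dependent variable, "having group (BFR-RT and CTRL) and time (0 W, 12 W and 24 W") "as fixed factors, and participants as random factors". Participant is the only random term named. No residual covariance structure, group-by-time term, model contrast or degrees-of-freedom method is given.

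The same section says that "within-group (0-12 W and 0-24 W changes) and between-group effect sizes will be calculated" with Cohen's d. This is the only place where particular changes are named, and it concerns effect sizes, not model tests. On multiplicity, "Adjusted *p* values will be calculated using Hommel’s procedure", with unadjusted values reported as well. On software, "Statistical analysis will be carried out using SAS 9.3 software".

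The Abstract gives the size: "Thirty participants will be randomly distributed between 1) BFR-RT and 2) control (CTRL"). The Aims section lists retention of the effect 12 weeks after training stops, without naming the test. No correlation, standard deviation, significance level or power appears in the article.

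**The concern.** A participant effect plus an independent residual forces the same variance at 0, 12 and 24 W and the same correlation between every pair of visits. With complete data, each change is then judged against the average of the three pairwise change variances, whatever its own variance is.

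The three visits are not obviously exchangeable. They are a pre-training measurement, a post-training measurement and one after 12 weeks without intervention, and 0 W and 24 W lie twice as far apart as neighbouring visits. Correlation may fall with distance, or the trained visit may be the odd one out. In either case the pooled error is too small for some changes and too large for others. At stake are the level of the tests of the training effect and of its retention, and power at 12 W in a trial of 30.

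**Working it through.** The article states no error rate or power for this model, so there is no figure of its own to reproduce.

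**Inputs from the article.** N = 30, two groups, three visits, participant as the only named random factor.

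**Assumed.** 15 per arm, two-sided 0.05 before Hommel adjustment, complete normal data, group-by-time terms in the model, and the correlations and SDs shown below.

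**Formulae.** Write V(i,j) = s_i² + s_j² − 2·ρ_ij·s_i·s_j for the variance of the change between visits i and j, and V̄ for the mean of the three.
- The between-group difference in change has true variance 2V(i,j)/15.
- The random-intercept model takes 2V̄/15, with 2(N − 2) = 56 df.
- With k = V(i,j)/V̄, the actual level is approximately P(|t56| > 2.003/√k).
- For first-order autoregressive decay with adjacent correlation r and equal variances, k = 3(1 + r)/(3 + r) for 0-24 W and 3/(3 + r) for 0-12 W. At r = 0.8 these are 5.4/3.8 = 1.42 and 3/3.8 = 0.79.

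**Worked example.** Correlations are listed as 0-12 / 0-24 / 12-24 W. For 0.9/0.8/0.9 with SD 1, the change variances are 0.2, 0.4 and 0.2, with mean 0.267.
- 0-24 W: k = 0.4/0.267 = 1.5; 2.003/√1.5 = 1.64; level about 10.7%.
- 0-12 W: k = 0.2/0.267 = 0.75; 2.003/√0.75 = 2.31; level about 2.4%.

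**Levels by formula, confirmed by simulation** (40,000 trials per pattern; Monte Carlo error about 0.1 point at a level of 5%):

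| Assumed pattern | k, 0-12 W | level, 0-12 W | k, 0-24 W | level, 0-24 W |
|---|---|---|---|---|
| Equal correlation 0.8, equal SD | 1.00 | 5.0% | 1.00 | 5.0% |
| 0.9/0.85/0.9 | 0.86 | 3.5% | 1.29 | 8.3% |
| 0.9/0.8/0.9 | 0.75 | 2.4% | 1.50 | 10.7% |
| 0.9/0.7/0.9 (steep decay) | 0.60 | 1.2% | 1.80 | 14.1% |
| 0.8/0.9/0.8 (trained visit differs) | 1.20 | 7.3% | 0.60 | 1.2% |
| Correlation 0.8, SD 1/1.3/1 | 1.13 | 6.5% | 0.74 | 2.4% |

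The simulated levels agree to within about 0.3 points. Under autoregressive decay the simulated 0-24 W level is 8.2% at r = 0.5, 10.0% at 0.8 and 10.7% at 0.9.

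**Power at 12 W for a 0.4 SD effect.** A contrast-specific variance (28 df) gives about 66% when the 0-12 W correlation is 0.9. The pooled error gives about 61% for 0.9/0.85/0.9 and 56% for 0.9/0.8/0.9, a loss of roughly 4 to 10 points. One more severe pattern, 0.9/0.7/0.8, gives 36%.

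**Other tests of retention under autoregressive decay.** The 12-24 W change has a level of 2.6 to 3.5%, which is conservative. The overall group-by-time F test has 5.3 to 6.0%. For groups compared at 24 W with equal variances, the model's total variance is right and there is no inflation.

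**The alternative.** With complete data, an unstructured covariance gives each change its own variance. Its simulated level stays at about 5% for both changes in every pattern. Under truly equal correlation of 0.8, power is 38 to 39%, against 39 to 40% for the pooled error.

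**The case against.** The strongest reply is that the article does not say the participant effect is the only covariance term. SAS allows a random participant effect together with a structured residual. Residual structure and degrees of freedom commonly belong in the analysis plan, which is not shown. That stands as a limit: a reader might infer that the sponsor has ruled out any other structure, and the text does not support that. It does not remove the point, because the article lists the model's terms, and those terms taken as listed give compound symmetry.

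The reply also holds that the retention test is not named. This is correct. A reader might infer that the false-positive rate of the retention test doubles. That is true only if retention means the 0-24 W change and if correlation decays strongly enough.

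Finally, it holds that the direction of error depends on the chosen pattern. This too is correct. Growing spread after training does not by itself make 24 W too lenient: raising the SD equally at 12 and 24 W leaves both levels near 5%, and raising it at 12 W alone makes 0-12 W the lenient test. The reversed patterns weaken any claim that retention is declared too easily. They also show that the pooled error can fail either way, while the contrast-specific variance does not.

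**Conclusion.** The point holds in a limited form. The model as described implies one pooled error for all changes, and its tests of individual changes keep their level only if the visits behave exchangeably. Under assumed mild to moderate decay, the 0-24 W change test runs at about 8 to 11%, and up to about 14% with steep decay. The 0-12 W test is then conservative, at about 2.5 to 3.5% for mild to moderate decay. Under other patterns 0-12 W runs at about 6 to 7.5% and 0-24 W at 1 to 2.5%. Under equal correlation with equal variances both hold 5%.

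Hommel's procedure does not correct this, because it acts on p values that are already too small or too large. The documents do not support a statement that retention will be declared too easily, or that power at 12 W will be lost; both depend on correlations that the article does not give. The figures rest on the assumptions listed with the calculation. This is a change worth making before analysis, with medium confidence.

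**What to change.** State in the Data analysis section that the repeated measurements are modelled with an unstructured covariance over 0, 12 and 24 W, in place of the participant random intercept. In SAS PROC MIXED this is REPEATED time / SUBJECT=participant TYPE=UN, with DDFM=KR for Kenward-Roger degrees of freedom. Include the group-by-time terms, and name the between-group contrasts for the 0-12 W and 0-24 W changes as the estimates taken from the model, saying which one addresses retention.

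The cost is a sentence of text, a line of code and four more covariance parameters (six instead of two). If correlations and variances really are equal, about 1 to 2 points of power are lost. The article reports recruitment as ongoing at submission, so the change could be made before the data are analysed. If the analysis plan already sets such a structure, align the article's wording with it; nothing else is needed.

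### In the non-normal branch the only post-baseline test named is the Friedman test, which has no group term, so outcomes failing Shapiro-Wilk get no BFR-RT versus CTRL test or interval

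*Protocol article*

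**What the plan says.** The Data analysis section of the protocol article sets up two routes. The switch between them is a normality test: "Following visual inspection, data normality will be assessed using the Shapiro-Wilk test".

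- **Normal route.** After a baseline check, a mixed model is fitted to each dependent variable, "having group (BFR-RT and CTRL) and time" as fixed factors and participant as random factor.
- **Non-normal route.** Kruskal-Wallis is used at baseline only, and then: "Then, the Friedman test will be used to analyze repeated measures". The Methods paragraph of the Abstract repeats this: "Next, the Friedman test will be used to analyze repeated measures".

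Twelve dependent variables are listed: Child-Pugh class, MELD, SF-36, FSS, dietary records, TUG, 6MWT, SRT, 1-RM, CSA, PA and FL. 1-RM and CSA are the primary outcomes.

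Two further steps apply on either route. Within-group "and" between-group standardized differences are planned for every outcome ("between-group effect sizes will be calculated using Cohen’s" *d*), and p values are corrected for multiplicity ("Adjusted *p* values will be calculated using Hommel’s procedure").

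**The concern.** The trial randomizes patients so that BFR-RT can be compared with a sham relaxation control. The Friedman test ranks the three visits within each participant and asks whether the visits differ. Group is not one of its inputs. An outcome sent down the non-normal route therefore loses the test of the randomized contrast.

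There are two ways to run it, and neither recovers that contrast. Pooled over arms, it responds to any change common to everyone, such as learning of the test, attention or regression to the mean. Run separately in each arm, it invites the reading that BFR-RT worked because its own p value is below 0.05 and that of CTRL is not, which is not a test of the difference between arms. It also needs all three visits from each participant.

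The Hommel-adjusted set of p values would then mix group-related hypotheses with time-only hypotheses. This is not a detail left to a fuller document: the article names the fallback test twice, and that test cannot answer the trial's question.

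**Working it through.** The defect is structural. The article gives no figure to reproduce here, so the numbers below only show its reach and consequence.

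**1. Does the Friedman test use group?** A table of 30 participants by 3 visits was analysed before and after shuffling participants across arms. The statistic was 0.867 (p = 0.648) both times. It carries no information on BFR-RT versus CTRL.

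**2. What else in that route tests group after baseline?** Kruskal-Wallis is confined to baseline values. Cohen's *d* between groups is an effect size, with no test or interval stated. Nothing else is named.

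**3. How often could the gate fire?** The level of the Shapiro-Wilk test is not stated; 0.05 is assumed.

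- Two primaries, if truly normal and independent: 1 − 0.95² = 0.0975, about 10%.
- Child-Pugh class: the eligibility criteria exclude class C, which leaves at most two levels at baseline. Shapiro-Wilk on 30 values with 1, 2, 3, 5, 8 or 15 patients in the second class gives p < 0.000001 each time. With none in the second class all values are identical, and the software returns p = 1 with a zero-range warning.

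**4. What happens when both arms change equally and treatment does nothing?** Assumed inputs: 15 per arm (the article gives 30 in total and no ratio), normal data, the same shift at 12 W and 24 W in both arms, 0.05 level. Correlations are either 0.8/0.7/0.8 or 0.5 throughout. Results of a check with 4,000 runs per row:

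| Correlations | Shared change | Pooled Friedman rejects | BFR-RT significant, CTRL not | Exactly one arm significant |
|---|---|---|---|---|
| 0.8/0.7/0.8 | 0.3 SD | 53% | 19% | 38% |
| 0.8/0.7/0.8 | 0.2 SD | 28% | 11% | 24% |
| 0.8/0.7/0.8 | 0.1 SD | 11% | 6% | 13% |
| 0.5 | 0.3 SD | 30% | 12% | 26% |
| 0.5 | 0.2 SD | 16% | 7% | 15% |
| 0.5 | 0.1 SD | 8% | 5% | 11% |

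Repeat simulations of the same scenarios differ by a point or two.

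**5. Would a between-arm rank test behave better?** A second simulation used log-normal data, within-person correlation 0.7, 15 per arm and 2,000 runs (all assumed). It compared pooled Friedman with a Mann-Whitney test of the 0 W to 12 W change on the log scale.

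| Change in BFR-RT / CTRL (SD, log scale) | Pooled Friedman rejects | Mann-Whitney rejects |
|---|---|---|
| 0 / 0 | 6% | 5% |
| 0.5 / 0.5 | 87% | 5% |
| 0.8 / 0 | 57% | 71% |
| 0.8 / −0.8 | 1% | 100% |

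The Friedman test rejects when the arms do not differ (second row) and misses arms that move in opposite directions (last row). The Mann-Whitney test does neither.

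**The case against.** Several points on the other side are sound.

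- **A comparison does remain.** A reader might infer that these outcomes get no BFR-RT versus CTRL comparison at all. The article does not support that: between-group Cohen's *d* is planned for each outcome with no restriction to the normal route. A change shared equally by both arms would tend to give a *d* near zero, reported beside the Friedman p value. What is missing is a test or interval. Since *d* rests on means and SDs, it is also an awkward sole summary for data just declared non-normal.
- **Child-Pugh class is not certain to fail.** A reader might infer certainty from the exclusion of class C. The Eligibility criteria admit class B, but the limitations paragraph of the Discussion describes class B as excluded too. If all patients were class A, the baseline variable would be constant and the gate would not reject. The claim is conditional, and the two passages must be reconciled.
- **A figure across all 12 variables says little.** 1 − 0.95¹² = 46% is the chance of at least one false rejection if all 12 are normal and independent. Class, score and count variables are not normal, and measures on the same muscle are not independent. Nothing shows that 1-RM or CSA will fail.
- **The simulation inputs are assumed.** With correlation 0.5 or a 0.1 SD change the rates fall well below the highest row. They give a direction and a range, not a forecast.

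None of this touches the central point: on the non-normal route no post-baseline test involves group.

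**Conclusion.** The point holds in this form: an outcome that fails Shapiro-Wilk is left without a hypothesis test or interval for BFR-RT versus CTRL, and this follows from the named test without any numerical assumption. The defect is conditional on the gate firing. It can reach a primary outcome (about 10% by chance alone, under the normality, independence and 0.05 assumptions above). It will reach Child-Pugh class, which the Discussion uses to judge safety, if both A and B patients are enrolled. Under the assumed inputs in step 4, the size of the misleading signal ranges from near the nominal level (8% pooled) to 53%. Arm-wise testing favours BFR-RT alone in about 5% to 19%. It should be corrected before analysis, because the fallback cannot serve the purpose of the randomization and the change is cheap.

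**What to change.** Replace the Friedman test with a between-arm method.

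1. Fit the planned mixed model to every continuous outcome whatever the Shapiro-Wilk result. State the group-by-time term explicitly, report BFR-RT minus CTRL contrasts with intervals at 12 W and 24 W, and check residuals rather than raw data.
2. Name in advance one rank-based between-arm analysis of change from baseline, for example Mann-Whitney with a Hodges-Lehmann interval, and say whether it is the fallback or a sensitivity analysis. If it is the fallback, state what triggers it, so that one loosely defined switch is not exchanged for another.
3. Analyse Child-Pugh as points, or as the proportion worsening by arm with an exact interval.
4. Reconcile the Eligibility criteria and the Discussion on whether class B patients are included.
5. Make the same correction in the Abstract, and apply Hommel's procedure to the between-arm p values only.

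The cost is analysis wording. No extra patients, visits or measurements are needed, and recruitment was still ongoing when the article was submitted.

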### Design overview

This study is an experimental approach with repeated measures for data collection to investigate the efficacy and safety of a BFR-RT protocol in LC patients (Additional file 1 - SPIRIT 2013 Checklist) (Fig. 1). All participants (target *n* = 30) will be evaluated at three time points: before the training period (0 W), after 12 weeks (12 W), and at follow-up (24 W). Participants will be randomly allocated between a training (BFR-RT) and control (CTRL) group. Both groups will undergo their respective interventions two times per week for 12 weeks, followed by a no-intervention period of 12 weeks to verify the interventions carryover effects (Fig. 2).

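### Outcomes judged non-normal go to the Friedman test, which has no group term, so they get no between-arm hypothesis test after baseline, only a descriptive Cohen's d

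*Protocol article*

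**What the plan says.** The trial is a two-arm randomised comparison. The Design overview states: "Participants will be randomly allocated between a training (BFR-RT) and control (CTRL) group".

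The Data analysis section sets up two routes, chosen by a normality check: "Following visual inspection, data normality will be assessed using the Shapiro-Wilk test".

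- **Normal route.** A mixed model is fitted to each dependent variable, "having group (BFR-RT and CTRL) and time (0 W, 12 W and 24 W) as fixed factors, and participants as random factors".
- **Non-normal route.** First, "In case of non-normal data distribution, a Kruskal–Wallis test will be implemented to test for differences in baseline values". After that, "Then, the Friedman test will be used to analyze repeated measures". The abstract's Methods paragraph gives the same fallback: "Next, the Friedman test will be used to analyze repeated measures".

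The list of dependent variables ends with "TUG, 6MWT, SRT, 1-RM, CSA, PA and FL", so both primary outcomes (1-RM and CSA) are subject to the routing. The same section adds that "between-group effect sizes will be calculated using Cohen’s *d* [33] for each outcome", without limiting this to either route. It also plans Hommel-adjusted p values for all variables.

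**The concern.** The Friedman test is a one-factor, within-participant rank test. It asks whether the visits differ and makes no use of allocation. On the normal route, group is a fixed factor. On the non-normal route, group appears in a test only at baseline, before any treatment has been given.

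The plan does not say whether Friedman would be run on all participants together or within each arm. Neither answers the trial's question:

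- **Pooled**, it tests a time trend common to both arms. Familiarity with the test or drift in the disease would count as a positive result even if BFR-RT did nothing.
- **Per arm**, it invites the reading that BFR-RT worked because its p value is below 0.05 and that of CTRL is not. A contrast of two p values is not a test of the difference between arms.

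At stake is the p value for the treatment effect on any outcome routed this way, a primary outcome included.

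**Working it through.** The document gives no power, alpha or effect size tied to this test, so there is no stated figure to reproduce. The check concerns what the test can detect.

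**Inputs.** From the document: 30 participants, two arms, three visits (0 W, 12 W, 24 W). Assumed: 15 per arm, two-sided 0.05, and the correlations, changes and skewness given below.

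**1. The statistic itself.** With n participants, k visits and visit rank sums R_j,

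Q = [12 / (n k (k+1))] × ΣR_j² − 3n(k+1).

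For n = 30 and k = 3, 12/(30×3×4) = 1/30 and 3×30×4 = 360, so Q = ΣR_j²/30 − 360. No term carries the arm. Two extreme cases show what follows:

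- *Arms move in opposite directions.* All 15 in BFR-RT rank their visits 1, 3, 2 and all 15 in CTRL rank them 3, 1, 2. The rank sums are 15+45 = 60, 45+15 = 60 and 30+30 = 60. Then ΣR_j² = 3×3,600 = 10,800 and Q = 360 − 360 = 0, although the arms differ completely.
- *Arms move identically.* All 30 rank their visits 1, 3, 2. The rank sums are 30, 90 and 60. Then ΣR_j² = 900 + 8,100 + 3,600 = 12,600 and Q = 420 − 360 = 60 on 2 degrees of freedom. This is overwhelmingly significant, with no difference between arms.

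As a numerical check, shuffling the 30 rows of a simulated data set left the result unchanged (chi-square 1.867, p = 0.393 both times).

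**2. Size in less extreme cases.** Simulated trials used 15 per arm, normal visits and common correlation 0.8 to 0.9. Changes are in SD units and the same at 12 W and 24 W. The rank-sum test is Mann–Whitney on the 0-12 W change.

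| Scenario | Pooled Friedman significant | Per-arm Friedman: BFR-RT significant, CTRL not | Rank-sum on change |
|---|---|---|---|
| No treatment effect, both arms +0.1 | 13% to 18% | 7% to 9% | about 5% |
| No treatment effect, both arms +0.3 | 61% to 89% | 21% to 24% | 4% to 5% |
| True difference 0.5: BFR-RT +0.25, CTRL −0.25 | 4% to 5% | not tabulated | 51% to 81% |
| True difference 0.5: BFR-RT +0.5, CTRL 0 | 41% to 62% | not tabulated | 51% to 81% |

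The rank-sum test depends only on the difference between arms, so one range serves both 0.5 SD rows. A repeat run agreed to within about 2 percentage points.

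The pattern does not depend on normal data. With log-normal data and correlation 0.7, pooled Friedman rejected in 90.2% of runs when both arms changed by 0.6 SD at 12 W. It rejected in 2.2% when the arms changed by +0.6 and −0.6 SD. The rank-sum test rejected in 5.2% and 96.3%.

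**3. How often the route is used.** The article gives no spread or skewness for any outcome and no level for Shapiro–Wilk. At an assumed 0.05 level and n = 30, Shapiro–Wilk rejects log-normal data in about 9% of samples at log-SD 0.1, 18% at 0.2, 36% at 0.3 and 72% at 0.5. At n = 15 the corresponding figures are about 6%, 10%, 20% and 39%. Truly normal data are sent there 5% of the time per outcome. For at least one of two primaries, if independent, this is 1 − 0.95² = 9.8%.

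**The case against.** **The arms are still compared.** A reader might infer that outcomes on this route are never compared between arms, or that the randomised comparison is lost altogether. The document does not support that. It plans a between-group Cohen's d for each outcome, and Kruskal–Wallis can compare the arms at baseline. This objection stands and sets the limit of the point. It does not remove it: d is a ratio of means to SD, poorly suited to data just judged non-normal, and no interval or test is stated for it.

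**The defect is conditional.** Nothing in the document shows that 1-RM or CSA will fail the normality check, and the 9% to 72% range rests on assumed skewness. This stands too. It would be wrong to say that the primaries will lose their test.

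**The scenarios can be chosen to look bad.** Exactly opposite changes are the worst case for a pooled test. If only BFR-RT gains, pooled Friedman does reject in 41% to 62% of trials, so a true benefit is not always missed. Even so, that rejection is evidence of a time trend and not of a difference between arms.

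**Mixed hypotheses under Hommel.** A reader might infer that combining Friedman and model p values invalidates the adjustment. It does not: a family may contain different hypotheses, and the article does not say which p values enter. The narrower issue is that a time-only p value should not stand for the treatment effect.

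**A fuller plan may exist.** It could add a test. However, the article does not leave the method open. It names Friedman as the repeated-measures analysis, in both the abstract and the Data analysis section.

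**Conclusion.** The point holds in this form: on the non-normal route, the only test after baseline is one that cannot see treatment group. Outcomes sent there, possibly including both primaries, have no between-group hypothesis test after baseline and keep only a descriptive Cohen's d. That follows from the form of the test and rests on no assumption.

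The size does rest on assumptions. With 15 per arm and visit correlation 0.8 to 0.9, a change shared by both arms gives a significant pooled Friedman result in 13% to 18% of trials (0.1 SD) or 61% to 89% (0.3 SD) when there is no treatment effect. A true 0.5 SD difference is flagged in anything from about 4% to 62% of trials, depending on how the change is split between the arms. How often the route will be taken cannot be determined from the document. The point merits correction because it can reach a primary outcome, the method is stated rather than left open, and the remedy is cheap.

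**What to change.** In the Data analysis section and the abstract's Methods paragraph, replace Friedman as the inferential test with a between-arm rank method. One suitable form is a rank-sum test of BFR-RT against CTRL on the 0-12 W change and on the 0-24 W change, each with the Hodges–Lehmann difference and 95% CI. A rank-based group by time analysis is an equally acceptable choice. Outcomes with few levels, such as Child-Pugh class, will have many ties and need a tie-corrected or exact version.

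Stratification by allocation quartile is optional. The Randomization section forms quartiles from 1-RM and CSA without saying how the two combine. Strata would hold about 30/4 = 7.5 participants, or about 30/16 = 1.9 if the two sets of quartiles were crossed.

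Use the between-arm p values as the treatment-effect p values in the Hommel adjustment, and keep any Friedman result as within-arm description.

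The cost is a few sentences and a few lines of code, with no new participants, visits or measurements. The change should be dated and made before outcome data are compared by arm.
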